## Abstract

**Background:**

The treatment of idiopathic full-thickness macular holes involves surgery to close the hole. Some surgeons advise patients to adopt a face-down position to increase the likelihood of successful macular hole closure. However, patients often find the face-down positioning arduous. There is a lack of conclusive evidence that face-down positioning improves the outcome. The ‘Positioning In Macular hole Surgery’ (PIMS) trial will assess whether advice to position face-down after surgery improves the surgical success rate for the closure of large (≥400 μm) macular holes.

**Methods/design:**

The PIMS trial is a multicentre, parallel-group, superiority clinical trial with 1:1 randomisation. Patients (*n* = 192) with macular holes (≥400 μm) will be randomised after surgery to either face-down positioning or face-forward positioning for at least 8 h (which can be either consecutive or nonconsecutive) a day, for 5 days following surgery. Inclusion criteria are: presence of an idiopathic full-thickness macular hole ≥400 μm in diameter, as measured by optical coherence tomography (OCT) scans, on either or both eyes; patients electing to have surgery for a macular hole, with or without simultaneous phacoemulsification and intraocular lens implant; ability and willingness to position face-down or in an inactive face-forward position; a history of visual loss suggesting a macular hole of 12 months’ or less duration. The primary outcome is successful macular hole closure at 3 months post surgery. The treatment effect will be reported as an odds ratio with 95% confidence interval, adjusted for size of macular hole and phakic lens status at baseline. Secondary outcome measures at 3 months are: further surgery for macular holes performed or planned (of those with unsuccessful closure); patient-reported experience of positioning; whether patients report they would still have elected to have the operation given what they know at follow-up; best-corrected visual acuity (BCVA) measured using Snellen charts at a standard distance of 6 m; patient-reported health and quality of life assessed using the National Eye Institute Visual Function Questionnaire (VFQ-25).

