### Main objectives

The PIMS trial aims to determine whether the advice to position face-down improves the surgical success rate for closure of large (≥400 μm) macular holes, and thereby reduces the need for further surgery. This trial will benefit patients by providing robust evidence on the value of posturing following surgery for large macular holes, and enable health care providers and patients to make an informed choice for the best positioning to adopt after surgery.

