## Outcome measures

The primary outcome of the study is the anatomical closure of the macular hole at 3 months post surgery.

Successful closure of the macular hole will be determined by OCT scans. The scans will be anonymised and sent to two independent retinal surgeons who will independently grade the macular hole as closed; ‘open and flat’ (without a cuff of subretinal fluid); or ‘open and elevated’ (with cuff of subretinal fluid). The readers will be masked to the identity and allocated treatment of the subject. In the event of any disparity in grading, a third independent retinal surgeon, also masked to identify and treatment allocation, will arbitrate.

The categories ‘open and flat’ (without a cuff of subretinal fluid), or ‘open and elevated’ (with a cuff of subretinal fluid) will be pooled into one category of ‘open’ for the purpose of analysis.

Secondary outcomes at 3 months post surgery are:Further surgery for macular holes, performed or planned (yes/no)Best-corrected visual acuity (BCVA) measured using a Snellen chart at a standard distance of 6 mPatient-reported experience of positioning on a scale from 0 (very difficult) to 10 (very easy)Patient-reported health and quality of life assessed using the National Eye Institute Visual Function Questionnaire (VFQ-25) from 0 (worst health and quality of life) to 100 (best health and quality of life)Patient-reported outcome ‘Given what you now know, would you still have elected to have the operation?’ with responses Yes, No or Don’t Know

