### Sample size

Clinical consensus is that face-down positioning would be recommended if there were a difference of 15% in success rates. This is the smallest clinically relevant treatment difference that we wish to detect. Previous research [6] indicates that successful closure of large macular holes without advice to position face-down occurs in 80% of cases. A study with 86 patients per group has 85% power and 95% confidence to detect a difference in outcome rate of 80% in the face-forward positioning arm versus 95% in the face-down positioning arm. With an anticipated 10% loss to follow-up, we are aiming to recruit 96 patients in each arm.

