## Analysis methods

### General analysis principles

The primary analysis for each outcome will be by intention-to-treat, meaning that all patients on whom an outcome is available will be included in the analysis, and will be analysed according to the treatment group to which they were randomised.

Through vigilance and careful planning, the PIMS trial management team aim to achieve complete capture of all data from all patients, including patients who do not adhere to the protocol or patients who withdrawal from the trial. We acknowledge that despite our best efforts, some patients may have missing data. In accordance with the intention-to-treat principle and to avoid concerns over data-driven selection methods, we state the plan for dealing with missing data here.

Missing data is a potential source of bias, and the extent and pattern of missing data can influence the interpretation of the trial. The sample size for the PIMS trial allows for a 10% loss of follow-up, and in our results we will provide a full listing of all the reasons for patients’ withdrawal of the study. This list will be helpful in justifying the assumptions that we make in regards to missing data; however, we cannot be certain that there is a relationship between observed covariates and missing outcome data, and cannot exclude the possibility of some data missing not at random.

We will analyse the data without undertaking any sensitivity analysis if the primary outcome is missing in fewer than 5% of cases (nine patients or less). If more than nine patients’ primary outcome is missing, we will undertake sensitivity analysis to test if the missing at random assumptions are appropriate. We will use a pattern-mixture approach to model the consequences of a systematic difference between missing and nonmissing values, to see if the conclusions drawn from the PIMS study are affected when the missing-at-random assumption is violated.

All analyses will be performed using Stata (Stata Corporation, College Station, TX, USA).

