### Variables measured and schedule of assessments

The variables measured preoperatively are age, sex, ethnicity, laterality, duration of symptoms, BCVA (Best-corrected Visual Acuity), lens status (either phakic or pseudophakic), macular hole diameter on OCT scans and the Quality of Life VFQ-25 questionnaireThe variables measured at 3 months postoperatively are BCVA, macular hole status (closed; open flat or open elevated), the Quality of Life VFQ-25 questionnaire, subject-reported experience of positioning and, if primary repair of a macular hole failed, was a second operation performed or planned?

For each comparison of outcomes according to positioning policy, the following summaries will be provided (see templates for tables in Additional file 1):The number of patients in each positioning policy group who are included in the analysisA summary measure of the outcome, by positioning policy group (mean and standard deviation (SD) for continuous outcomes, number and percentage in each category for categorical outcomes). The treatment effect (difference in means for continuous outcomes, odds ratio for binary outcomes) with its 95% confidence interval (95% CI) and *p* value

All comparisons will adjust for linear effect of macular hole size (μm) at baseline, phakic lens status at baseline, and a random effect of site (hospital). We will anonymise data reported by hospital site. Outcomes which are also assessed at baseline (BCVA and quality of life) will be analysed adjusting also for a linear effect of the baseline measurement.

Patients have a 2-week postoperative appointment, at which time clinicians may be able to identify that the macular hole closure was unsuccessful, meaning that a second operation to close the hole is required. The outcome of any participant who had a second surgery after randomisation but before the 3-month visit will be imputed as open, as it is most unlikely that the hole will close without further treatment by 3 months. These patients will not be completing secondary questionnaires.

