### Analyses of secondary outcomes

For the analysis of further surgery for macular holes, performed or planned, we will use logistic regression (*xtlogit*). Best-corrected visual acuity (BCVA), measured using Snellen charts at a standard distance of 6 m, will be transformed to a LogMAR scale with two decimal places [9], and then analysed using linear regression (*xtreg*). Measurements of BCVA corresponding to count fingers (CF), hand movements (HM), perception of light (PL), and no perception of light (NPL) will be replaced with values of 2.10, 2.40, 2.70, and 3.00, respectively. The number of patients in each BCVA category and their corresponding numerical values will be tabulated by treatment arm. For the patient-reported experience of positioning at 3 months, which is on the scale 0 (very difficult) to 10 (very easy) we will remain masked to treatment arm and consider an applicable cut-off value to dichotomise this variable and then use logistic regression (*xtlogit*). For the patient-reported outcome ‘Given what you know now, would you still have elected to have the operation?’ we will pool the responses ‘Don’t know’ and ‘No’ into one category, and use logistic regression (*xtlogit*). If the proportion of ‘Don’t know’ responses exceeds 10% (19 patients) we will undertake a sensitivity analysis by pooling the ‘Don’t know’ with ‘Yes’ responses and compare how this alternative pooling affects the odds ratio estimate. The Complications of Age-related Macular Degeneration Prevention Trial Research Group [10] observed a skewed distribution of the VFQ-25 score; therefore, we will assume that our results will be similarly skewed, and perform a logistic transformation (log(x/(100 − x))) of the VFQ-25 scores, and with this transformed outcome use linear regression (*xtreg*). When adjusting analyses of BCVA and VFQ-25 for their respective baselines we will use the same normalising transformation for the baseline measurement as for the follow-up measurement.

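### The plan is inconsistent on who is analysed for further surgery, and the restricted version would compare only patients selected on the primary outcome

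*SAP article*

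**What the plan says.** The SAP article describes this outcome in several places, and they do not agree on who is counted.

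- Abstract, Methods/design: "further surgery for macular holes performed or planned (of those with unsuccessful closure". This limits the outcome to failures.
- Outcome measures: "Further surgery for macular holes, performed or planned (yes/no". No limit is stated.
- Variables measured and schedule of assessments: the 3-month item is "if primary repair of a macular hole failed, was a second operation performed or planned". It is asked conditionally.
- Analyses of secondary outcomes: "For the analysis of further surgery for macular holes, performed or planned, we will use logistic regression". No denominator is given.

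Three other statements bear on the choice. General analysis principles says that "all patients on whom an outcome is available will be included in the analysis", in the group to which they were randomised. Main objectives asks whether face-down advice improves closure "and thereby reduces the need for further surgery". For early re-operations, Variables measured says "The outcome of any participant who had a second surgery after randomisation but before the 3-month visit will be imputed as open", so those patients always count as failures.

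**The concern.** Closure is the primary outcome and is observed after randomisation. If positioning affects closure, the patients left with an open hole in each arm have been selected by the treatment. Comparing re-operation among them is no longer a randomised comparison.

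It also answers a different question. Among failures, the odds ratio measures how readily surgeons and patients go on to a second operation once the first has failed. The stated objective is that fewer second operations are needed because more holes close. That effect acts through closure, and conditioning on failed closure removes it.

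The route to the restricted analysis is short. If the conditional item is blank for closed holes, an analyst who includes everyone with an available outcome arrives at the failures-only set described in the abstract. A trial that reduced further surgery substantially could then report an odds ratio near 1 for it, with a very wide interval or no estimate.

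**Working it through.** **Inputs from the Sample size section.** The design is built on "a difference in outcome rate of 80% in the face-forward positioning arm versus 95% in the face-down positioning arm", with 86 per group, 85% power, 10% loss and 96 recruited per arm.

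**The plan's own figure.** For two proportions, two-sided 5%, without continuity correction:

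n = [1.960 × √(2 × 0.875 × 0.125) + 1.036 × √(0.80 × 0.20 + 0.95 × 0.05)]² / 0.15² = (0.917 + 0.472)² / 0.0225 ≈ 85.7, so 86 per group.

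86 / 0.9 = 95.6, so 96 per arm. Both figures reproduce.

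**Size of the restricted set.** Face-forward: 86 × 0.20 = 17.2 failures. Face-down: 86 × 0.05 = 4.3. Together 21.5 of 172 patients, or 12.5%. The model has treatment, hole size, lens status and a random effect for nine hospitals, so there would be about 21.5 / 9 = 2.4 patients per hospital.

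**The two analyses compared.** Let q be the proportion of failures with further surgery performed or planned. The document does not give q, so it is an assumption, taken as equal in both arms and shown as a range.

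- All randomised: the rates are 0.20q and 0.05q. Their ratio is 4 for any q.
- Failures only: the rate is q in both arms. The odds ratio is 1 for any q below 1, and undefined at q = 1.
- The failures-only odds ratio cannot be estimated when either arm has all or none of its failures re-operated, or has no failures. With failure rate p, an arm has both outcomes present with probability 1 − (1 − pq)^86 − (1 − p(1 − q))^86 + (1 − p)^86. The chance of no estimate is 1 minus the product of this over the two arms.

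Example at q = 0.5:

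- Face-down: 1 − 2 × 0.975^86 + 0.95^86 = 1 − 0.227 + 0.012 = 0.785.
- Face-forward: above 0.999.
- No estimate: 1 − 0.785 ≈ 21%.

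| q (assumed) | All randomised, face-forward v face-down | Odds ratio | Power | Failures only: odds ratio | Fisher test rejects | No estimate |
|---|---|---|---|---|---|---|
| 0.5 | 10.0% v 2.5% | 0.23 | 53% | 1 | 2% | 21% |
| 0.7 | 14.0% v 3.5% | 0.22 | 71% | 1 | 2% | 31% |
| 0.8 | 16.0% v 4.0% | 0.22 | 78% | 1 | 1% | 46% |
| 0.9 | 18.0% v 4.5% | 0.21 | 83% | 1 | 1% | 72% |
| 1.0 | 20.0% v 5.0% | 0.21 | 88% | undefined | 0% | 100% |

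Power is for an uncorrected chi-square test with 86 per arm, by enumerating the binomial outcomes. The normal approximation that reproduces the plan's 86 gives 53%, 69%, 75%, 81% and 85% in the same rows. The Fisher column averages over the chance number of failures in each arm. It is a false-positive rate, since the true odds ratio is 1: this comparison has nothing to detect, whatever its size.

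**The case against.** A reader might infer that further surgery is defined only among failures throughout the plan, and that the trial therefore cannot show whether positioning reduces it. The document does not support that. Outcome measures, where outcomes are formally listed, has no restriction. The analysis section names no subset, and the intention-to-treat principle is stated for every outcome. The only restriction inside a definition is a parenthesis in the abstract. The conditional item reads naturally as a skip pattern: a patient whose hole closed had no reason for a second operation. Early re-operations are set to open, so they cannot fall outside the failures. The yes/no outcome can thus be derived for every patient with known closure status, and the all-randomised analysis is open to the trial.

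Two further objections have force. The failures-only odds ratio of 1 follows from assuming equal re-operation rates. With unequal rates it could lie on either side of 1, and the chance of no estimate depends strongly on the rate. Also, this is one of five secondary outcomes, and with closed holes coded No it largely repeats the primary; at q = 1 it is the same variable.

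These points limit the size of the finding but do not remove it. A stated restriction conflicts with the outcome list and the objective, and the analysis section does not settle it. Selection on a post-randomisation outcome is a fault at any value of q. Overlap with the primary outcome is what the objective implies, and is no reason to leave the denominator open.

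**Conclusion.** The plan contradicts itself on the denominator for further surgery, and one reading its text permits is not a randomised comparison. On the plan's own closure rates, that reading uses about 21 of 172 evaluable patients, split roughly 17 to 4, and cannot address the stated objective. For equal re-operation rates of 50% to 100%, a fourfold reduction would be analysed either with about 53% to 88% power or through an odds ratio that is truly 1 or undefined, with no estimate in about 21% to 100% of trials.

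The failure counts rest only on the plan's assumptions. The power and estimability figures also rest on the assumed re-operation rate, and they are unadjusted approximations to the planned mixed model. The harm arises only if the restricted reading is followed. The primary analysis is unaffected. This is a should-fix on a secondary outcome.

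**What to change.** - Abstract: delete the restriction to unsuccessful closures.
- Outcome measures and Analyses of secondary outcomes: state that the denominator is all randomised patients with a known outcome, analysed as randomised, and that a closed hole with no further surgery is coded No. Fit the planned logistic model to that set.
- Variables measured: state that the conditional item is a skip pattern and does not define an analysis population. A blank item for an open hole should be treated as missing, not as No.
- Report the number and proportion re-operated among failures by arm as a description only, with no odds ratio or p value.

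The cost is a few sentences of wording. No new data are needed. Recruitment was still open when the article was submitted, and the plan is described as signed off before database lock and before access to unmasked data, so the change could be made at that stage without knowledge of results by arm.

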**Discussion:**

The PIMS trial is the first multicentre randomised control trial to investigate the value of face-down positioning following macular hole standardised surgery.

**Trial registration:**

International Standard Randomised Controlled Trials Number registry, ID: ISRCTN12410596. Registered on 11 February 2015.

United Kingdom Clinical Research Network, ID: UKCRN17966. Registered on 26 November 2014.

**Electronic supplementary material:**

The online version of this article (doi:10.1186/s13063-017-2020-6) contains supplementary material, which is available to authorized users.

## Overview

### Purpose and scope of statistical analysis plan (SAP)

The aim of this paper is to report, in detail, the planned analyses that were approved by the Trial Steering Committee for the principal research for the PIMS (Positioning In Macular hole Surgery) trial, a multicentre, interventional, comparative, randomised controlled clinical trial comparing face-down with face-forward positioning on the outcome for surgery for large macular holes. The PIMS trial is registered with ISRCTN, number 12410596 and the UKCRN portfolio, number 17966. The pilot study preceding PIMS was published in *Eye*, 2011 [1]. This pilot randomised controlled trial (RCT) explored the feasibility of a definitive trial to determine the value of face-down positioning following vitrectomy, internal limiting membrane (ILM) peeling, and C_3_F_8_ gas tamponade for full-thickness macular holes, without simultaneous phacoemulsification. The PIMS study protocol was published in *Trials*, 2015 [2]. We aim to maximise transparency of the planned analysis with the intention of eradicating misreporting or selective reporting of the trial data. We have also considered any contingences, with regards to specifying alternative analysis plans if statistical models fail to converge.

This analysis plan was written, reviewed and signed off prior to database lock, and prior to any member of the trial team having access to unmasked trial data.

### Changes from the published protocol

The protocol published in *Trials* stated that the analysis for the primary outcome would be adjusted for age and sex as fixed effects, and site as a random effect [2].

Opinion leaders questioned whether age and sex were associated with successful macular hole closure. A brief literature review highlighted a relevant study which did not find a significant association between age or sex and successful macular hole closure [3].

At the suggestion of the independent Trial Steering Committee (TSC) the PIMS management team decided to remove age and sex as covariates and to specify instead that the primary outcome would be adjusted for macular hole size (μm) and phakic lens status, with site as a random effect.

## Background and trial design

Further details of the rationale, treatment polices and design of the PIMS study are given in the study protocol.

In summary, idiopathic macular holes (macular holes) cause patients’ central vision to be blurred or distorted. Macular holes have an estimated annual incidence of 8 per 1000 individuals per year [4].

Macular holes can be treated surgically by removing the vitreous gel from the eye (vitrectomy), peeling off the ILM and then injection of a temporary gas bubble into the back of the eye. Surgery is deemed successful when the macular hole is fully closed. The current lack of evidence with which to guide patients has led to a lack of consensus among clinicians and wide variation in clinical practice. Patients are understandably confused and distressed by uncertainty and inconsistent advice.

Some surgeons advise patients to adopt a face-down position for a period immediately following surgery with the aim of improving the outcome by maintaining contact of the gas bubble with the macular hole. The duration of the face-down position varies among surgeons. However, maintaining the face-down position can be arduous for patients [5] and is associated with serious adverse events. Furthermore, evidence that face-down position treatment policy increases the closure rates of macular holes is lacking.

### Main objectives

The PIMS trial aims to determine whether the advice to position face-down improves the surgical success rate for closure of large (≥400 μm) macular holes, and thereby reduces the need for further surgery. This trial will benefit patients by providing robust evidence on the value of posturing following surgery for large macular holes, and enable health care providers and patients to make an informed choice for the best positioning to adopt after surgery.

